### Recruitment and randomization

Patient recruitment began in November 2008, following approval by the ethical review committees of the participating hospitals. Participating surgeons make use of an 11-item checklist to determine patient eligibility. All patients who meet the study inclusion criteria are informed by the surgeon or nurse practitioner about the study, and are given an envelope containing an information letter, a consent form and the baseline questionnaire. Eligible patients receive a phone call by a member of the research team within a few days, in order to carry out the informed consent procedures and to administer the baseline questionnaire to consenting patients. Patients are then randomized to the RGCT or the UC group in a 2:1 ratio. The computerized randomization is stratified per hospital and blocked per 9 cases [37]. These 12 random allocation sequences are generated by an independent individual, are stored in computer files, and remain unknown to the researchers until the patient is randomized. The participant as well as the treating surgeon or nurse practitioner is informed about the randomization outcome. The researchers are blinded to randomization outcome at the time of the baseline assessments, but not at the follow-up assessments. This is due to the fact that the researchers are responsible for arranging appointments with the genetic counselor for those women assigned to the RGCT arm of the study.

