### Participants

The study sample will be composed of 255 women with a clinically confirmed, newly diagnosed primary breast cancer or ductal carcinoma in situ (DCIS) who meet at least one of the criteria for referral for genetic counseling and DNA analysis according to the Dutch Institute for Healthcare Improvement (CBO). These criteria are: (1) age at time of breast cancer diagnosis less than 35 years; (2) previous history of cancer in the contralateral breast, with the first breast cancer diagnosis at less than 50 years of age; (3) previous personal history of ovarian cancer; (4) a family history of ovarian cancer; (5) a first degree male relative with breast cancer; (6) breast cancer diagnosed under the age of 50 years, with a first degree relative diagnosed with breast cancer under the age of 50 years; (7) breast cancer diagnosed under the age of 50 years, with a relative with prostate cancer diagnosed under the age of 60 years; (8) breast cancer, with two or more relatives from the same side of the family diagnosed with breast cancer, where at least one family member (either the patient or a relative) was diagnosed under the age of 50 years; or (9) a proven *BRCA1/2 *mutation in the family. Women who meet one or more of these criteria are considered to have a 10% or greater chance of having a BRCA1/2 gene mutation [35,36]. Women are excluded from the study if they are younger than 18 years of age, lack basic fluency in the Dutch language, are incapable of understanding informed consent, or are diagnosed with a breast cancer recurrence or with metastastic disease. The patients are being recruited from 12 hospitals in the Amsterdam and Utrecht regions of the Netherlands.

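### A single fixed block of 9 per hospital in an open trial lets a tracking observer know about 18–21% of allocations in advance: an avoidable risk of selection bias

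*Protocol article*

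**What the plan says.** All the relevant facts but one are in the protocol article under Recruitment and randomization.

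- **Method.** "The computerized randomization is stratified per hospital and blocked per 9 cases". Only one block size is given. On the ratio, the section says: "Patients are then randomized to the RGCT or the UC group in a 2:1 ratio".
- **Strata.** Under Participants: "The patients are being recruited from 12 hospitals in the Amsterdam and Utrecht regions of the Netherlands". There is one sequence per hospital.
- **Before randomization.** "Participating surgeons make use of an 11-item checklist to determine patient eligibility". The surgeon or nurse practitioner then introduces the study to every woman who meets the criteria. These women next "receive a phone call by a member of the research team within a few days, in order to carry out the informed consent procedures"; the baseline questionnaire is taken at that point.
- **After randomization.** "The participant as well as the treating surgeon or nurse practitioner is informed about the randomization outcome". The researchers are unblinded as well, because "the researchers are responsible for arranging appointments with the genetic counselor for those women assigned to the RGCT arm of the study".
- **Safeguards.** An independent individual generates the sequences. They stay hidden from the researchers until each patient is randomized, and the researchers are blind to that patient's arm at her baseline assessment.

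**The concern.** Hiding the list protects the list itself. It does not stop anyone from working out the rest of a block from allocations already known. Once all 3 UC or all 6 RGCT places in a hospital's current block are used, every remaining place in that block is determined. The research team is the group best placed to see this: it learns each allocation after the event and makes the next consent call.

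The primary outcome is a surgical choice, and inclination towards it is partly visible before randomization. Eligibility includes a proven *BRCA1/2* mutation in the family. The Intervention section also describes women whose family history alone is reason enough for bilateral treatment. If such women were approached, or encouraged to consent, when an RGCT place was known to be next, the arms would differ at entry in the direction of the first hypothesis. Events are also few: on the rates under Sample size, 0.05 × 85 ≈ 4 in UC and 0.18 × 170 ≈ 31 in RGCT. A handful of steered women could therefore matter.

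**Working it through.** The article gives no figure for predictability, so there is none to reproduce.

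**Inputs.** Block of 9, ratio 2:1 (hence 6 RGCT and 3 UC) and 12 hospitals, from Recruitment and randomization and Participants. N = 255 for analysis and 306 expected before attrition, from Sample size. Assumption: the observer knows the block size and has followed every allocation in the hospital.

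**Complete block.** A place is determined when all places from it to the end of the block belong to one arm.

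- 9th: always, 1.
- 8th: (6·5 + 3·2)/(9·8) = 36/72 = 0.50.
- 7th: (6·5·4 + 3·2·1)/(9·8·7) = 126/504 = 0.25.
- 6th: (6·5·4·3)/(9·8·7·6) = 360/3024 = 0.119.
- 5th: 720/15120 = 0.048.
- 4th: 720/60480 = 0.012.
- 1st to 3rd: 0.

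The sum is 1.929 of 9, or 21.4%. The closed form agrees: 6/(3+1) + 3/(6+1) = 1.5 + 0.429 = 1.929. Full enumeration of the 84 possible blocks gives the same values.

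**Split by arm.** Known RGCT: 1.5/9 = 16.7% of all places, which is 1.5/6 = 25% of RGCT places. Known UC: 0.429/9 = 4.8% of all places.

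**Incomplete last blocks (equal hospitals).**

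- N = 255: 255/12 = 21.25 per hospital, or two full blocks plus 3.25 places. 2 × 1.929 + 0.25 × 0.012 = 3.860; × 12 = 46.3; 46.3/255 = 18.2%.
- N = 306: 306/12 = 25.5 per hospital, or two full blocks plus 7.5 places. 3.857 + (0.012 + 0.048 + 0.119 + 0.25) + 0.5 × 0.50 = 4.536; × 12 = 54.4; 54.4/306 = 17.8%.
- Simulated unequal hospital sizes give averages of 18% to 19%.

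**Overall guessing.** Always naming the arm with more places left in the block is right 72.8% of the time, against 66.7% for always naming RGCT.

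**Effect of mixed blocks.** This was simulated with 21 and 27 patients per hospital and an observer who knows the possible sizes but not their order. Determined allocations fall from 18–21% with fixed 9 to about 5–6% with sizes 6 and 9, and to about 2% with 6, 9 and 12.

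**Cost of excluding determined allocations.** In complete blocks 170 × (1 − 1.5/6) ≈ 128 RGCT and 85 × (1 − 0.429/3) ≈ 73 UC remain. Power for 18% versus 5%, two-sided 0.05 (sidedness assumed), with continuity correction:

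- 85 and 170: (0.13 − 0.0088 − 1.96 × 0.0456)/0.0378 = 0.84, which gives 80%, the article's figure.
- 73 and 128: (0.13 − 0.0108 − 1.96 × 0.0498)/0.0425 = 0.51, which gives just under 70%.

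**The case against.** The strongest reply is that predictability is not bias, and that this trial leaves limited room to exploit it.

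- **Surgeons.** A reader might infer that the surgeon who screens learns every allocation in the hospital. The article does not say so. It says that the treating surgeon or nurse practitioner is told the outcome, which naturally means for that patient. A surgeon who sees only some of the hospital's allocations cannot reliably count out a block. This stands, and the point therefore rests mainly on the research team.
- **Opportunity.** Eligibility follows a checklist, all eligible women are to be informed, the call comes within days, and surgery is pending. This also stands, but timing of the approach and the tone of a consent call remain open.
- **Motive.** Under Objectives and research hypotheses, RGCT is available in usual care, though rarely recommended or requested, and the Intervention section says UC patients may be referred or refer themselves. Anyone who wants rapid testing for a particular woman has another route. This weakens the motive without removing it.
- **Concealment and adjustment.** The hidden list and baseline blinding do not prevent counting. Covariate adjustment under Statistical analyses covers measured differences only, not unmeasured inclination towards bilateral surgery.
- **Block size.** Nine is three times the smallest 2:1 block, and the overall gain in guessing is only about 6 percentage points. Both are true, but the determined places are the ones that matter.

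**Conclusion.** The concern holds as an avoidable design weakness. With one fixed block size in an open trial, about 18–21% of allocations (about 46 of 255 with incomplete last blocks) could be known in advance, mostly RGCT places. This rests on an observer who knows the block size and tracks all allocations in a hospital. The researchers are placed to do the tracking; the article does not say whether recruiting staff know or use the block size.

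A reader might go further and conclude that the primary comparison is biased. The documents do not support that: nothing shows that selection occurred, and no shift in the 18% versus 5% contrast can be estimated from them. The sample size is not affected.

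**What to change.** For allocations not yet used, the independent individual should regenerate each hospital's list with block sizes varied at random among multiples of 3, for example 6, 9 and 12, all of which keep 2:1. The sizes and their order should be withheld from researchers and hospitals until recruitment closes. The cost is a short amendment and slightly more possible imbalance within small hospitals. Allocations already made cannot be repaired.

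An analysis of the primary outcome without the allocations that were fully determined under the old blocks may be reported, but only as an exploratory check. The report should say that it drops mainly RGCT women, that it would lower power from about 80% to just under 70% if all blocks had been of the old kind, and that partly predictable allocations stay in.

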### Intervention

Women in the RGCT group receive an appointment with a clinical geneticist or genetic counselor within one week following randomization, either at the Family Cancer Clinic of the Netherlands Cancer Institute/Antoni van Leeuwenhoek Hospital or at the Department of Medical Genetics of the University Medical Centre Utrecht. Those patients who decline to undergo RGCT are given the opportunity to receive genetic counseling and testing at a later time.

While the standard steps involved in genetic counseling are followed, the process is accelerated when necessary. All patients are asked to complete a standard, detailed family history form in order to draw a three-generation pedigree. Where possible, confirmation of the (age at) diagnosis of the affected family members is confirmed via medical record audits following required informed consent procedures. At the time of the first consultation with the clinical geneticist, the urgency of the steps to be taken are discussed and a decision about DNA testing is made. If the patient agrees, a blood sample for testing for mutations in the *BRCA1 *and *BRCA2 *genes can be taken on the same day. For women whose test result will not be of immediate consequence for their choice of treatment, the timing of the DNA testing does not need to be accelerated (i.e., DNA test results will be made available within 4 months). Examples are women who, from a medical point of view, cannot opt for breast conserving therapy and have already had a contralateral mastectomy, women who do not wish to take immediate secondary preventive measures, or women whose family history provides them with sufficient reasons to undergo bilateral treatment regardless of whether a mutation can be found.

Where it is anticipated that the DNA test results could influence treatment decisions, a fast-track procedure is used and the results are made available within 3 to 6 weeks. From a medical point of view, this timeframe is sufficiently short to inform patients and clinicians about the results before definite treatment decisions have to be made.

The number of contacts between the patient and the clinical geneticist prior to surgery depends on the complexity of each individual case. For women who choose not to undergo DNA testing, this may be limited to a single session. For women who undergo DNA testing, at least one additional session is held in order to discuss the DNA test results. All results of the RGCT are forwarded to the treating surgeon, and consultation between the clinical geneticist and surgeon takes place prior to and following the patient's first appointment with the clinical geneticist.

Psychosocial support is offered routinely to all women who opt for rapid DNA testing, *BRCA1/2 *carriers and to all women who are considering undergoing BLM regardless of whether they have undergone DNA testing. Where appropriate, referrals are made to mental health caregivers in the hospital. The need for and uptake of more intensive psychosocial care during subsequent treatment are being assessed as part of the study.

Women in the UC condition receive standard advice and care from their treating surgeon. In relation to the possible hereditary nature of their disease, this typically involves discussion of the family history and of appropriate surgical options. In some cases, patients may be referred for genetic counseling or may self-refer. However, in current practice, this occurs rarely during the pre-surgery period [38,39].

### Study measures

#### Sociodemographic and clinical data

The patients' age, education, marital status, ethnic background, work status and general health status are obtained via the baseline questionnaire. Data on family pedigree and genetic risk status are obtained via a questionnaire. Clinical data, including diagnosis, tumor characteristics and treatment history (surgical treatment, surgical complications, breast reconstruction, radiotherapy, adjuvant chemotherapy or hormonal therapy) are obtained via both questionnaire and medical record audit. Results of the genetic counseling and testing, including genetic test results, are obtained from the records of the participating departments of clinical genetics.

#### Choice of surgical procedure

The patients' definitive surgical treatment decision is determined via medical record audit. Via questionnaires women are asked to report the factors motivating their choice of treatment.

*Risk perception *is assessed with 4 items adapted from previous studies [40-42] that inquire about current perceived risk of recurrent or contralateral breast cancer (all questionnaires), of ovarian cancer, and of the possibility of having hereditary breast cancer (follow-up questionnaires). Women are asked to rate on a 5-point scale how likely they think it is that they will develop cancer again, and to rate their perceived risk on a continuous scale from 0% to 100%.

*Cancer worries *are assessed with 8 items, 6 of which are adapted from previous work by Watson [40,43], that measure the frequency of cancer-related worries, their impact on mood, and their impact on daily functioning.

The Hospital Anxiety and Depression Scale (HADS) [44] is used to assess *psychological distress. *The HADS contains 14 items. Both a total score and separate scores for anxiety and depression can be calculated. The HADS has been validated for use in the Dutch population, showing good psychometric properties, with Cronbach's alphas for both the anxiety and depression scales >0.70 [45-47].

*Cancer-specific distress *is assessed with the Impact of Events Scale (IES), a 15-item Likert-scale organized into 2 subscales: intrusive thoughts and feelings, and avoidance of thoughts and feelings related to the stressful situation. In this case, the stressful situation is the diagnosis of breast cancer [48]. The IES has high levels of internal consistency (alpha's above 0.80) and has been translated and validated for use in the Dutch setting [49].

*Satisfaction with decision-making *is assessed with the Satisfaction with Decision Scale (SWD) [50] and the Decisional Conflict Scale [51,52]. The 6-item SWD-scale can be adapted to any medical decision and, in this case, refers to the choice of surgical treatment. The scale has high internal consistency reliability (alpha = 0.86) [50]. The 16-item Decisional Conflict Scale contains three subscales: 'Uncertainty', 'Factors contributing' and 'Effective decision making'. The scale had high internal consistency reliability (alpha of the three subscales ranges from 0.75-0.82 in the Dutch version).

*Knowledge of breast cancer and its genetic aspects *is assessed with a 7-item, true-false-don't know questionnaire adapted from Claes *et al. *[14,53].

*Health-related quality of life *is assessed with the EORTC QLQ-C30 [54] and the EORTC breast cancer module, the QLQ-BR23 [55]. The QLQ-C30 includes 5 functional scales, 3 symptom scales, and a number of single item symptom measures. It is designed for use with a broad range of cancer patient populations. The QLQ-BR23 assesses breast cancer-specific symptoms, treatment side-effects, body image, sexuality and future perspective. Both questionnaires have been used extensively in studies of women with breast cancer, and exhibit good levels of reliability (alpha coefficients between 0.70 and 0.85) and construct validity.

#### Process-related variables

Perceived influence of the surgeon on treatment choice is assessed with a series of questions adapted from Schwartz et al. [24]. Women in the RGCT arm of the study are asked a series of study-specific questions about their experience and satisfaction with RGCT, and their perceived need for additional psychosocial care. Psychosocial care actually received is also being determined from the medical records and via self-report. The content of the professional psychosocial support received is also being assessed.

### Sample size

The sample size calculations are based primarily on the type of surgery chosen, and specifically on the uptake of bilateral mastectomy. With a total sample of 255 women (170 in the RGCT arm and 85 in the UC arm), the study will have 80% power to detect a difference of 18% versus 5% in the uptake of bilateral mastectomy, with the p-value set at 0.05. The sample size ratio of 2:1 was chosen to ensure that the RGCT sample is sufficiently large to obtain stable estimates of bilateral mastectomy and delayed prophylactic contralateral mastectomy uptake among *BRCA1/2 *carriers, and to allow for secondary analyses (e.g., to examine predictors of DNA testing uptake). The percentages indicated above are based on the following assumptions: (1) based on the participating hospitals' experiences in the previous three years, 5% of the women in the UC arm are expected to choose bilateral mastectomy; (2) in the RGCT arm, it is expected that 20% will test positive for a *BRCA1 *or *BRCA2 *mutation, of whom, on average, 50% will opt for a bilateral mastectomy. Of the remaining 80% of women in the RGCT arm, we expect a 10% uptake of bilateral mastectomy. For the remaining, primarily self-report outcomes (e.g., cancer worries and cancer-specific distress, decisional satisfaction, HRQL), the sample of 255 participants is more than sufficient to detect a 0.5 standard deviation between-group difference in mean scores. Based on data obtained from the cancer registries of the Integral Cancer Centers of Amsterdam and Middle Netherlands, and on data provided by the participating hospitals, it is estimated that there will be a total of 2550 newly diagnosed breast cancer patients during the recruitment period. Approximately 15% of these women is expected to be eligible for participation. Based on prior experience with recruitment of patients into similar studies, we expect an 80% response rate. This results in an expected N of 306 patients. This allows for an attrition rate of 17%, while retaining 255 women for the primary analysis.

### Statistical analyses

Analyses will first be performed to evaluate the comparability of the RGCT and the UC groups at study entry in terms of sociodemographic and clinical characteristics. Student's t-test or appropriate non-parametric statistics will be used, depending on the level of measurement. If the groups are not comparable on one or more background variables, those variables will be employed routinely as covariates in subsequent analyses. Between group differences in choice of surgery will be tested using the chi-square statistic or, if statistical adjustment is required for covariates, multiple logistic regression analysis. Analysis of (co)variance will be employed to assess group differences at 6 and 12 month follow-up in risk perception, psychological distress, knowledge, decisional satisfaction, and HRQL. Where appropriate, sociodemographic and clinical background variables, as well as baseline scores on the outcomes of interest, will be used as covariates. Effect sizes will be calculated using standard statistical procedures. Supplementary, descriptive analyses (both quantitative and qualitative) will be used for reporting the patients' experiences with RGCT. All primary analyses will, to as great an extent as possible, be conducted on an intention-to-treat basis. That is, all women in the RGCT group will be included in that group in the analyses, regardless of whether they actually carried through with RGCT. Supplementary analyses will be undertaken to examine sociodemographic, clinical and psychosocial factors associated significantly with (non-) attendance at the RGCT and uptake of BLM.

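### Baseline significance tests between the randomised arms choose the covariates and decide the form of the primary surgery test, so the primary analysis is not fixed in advance

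*Protocol article*

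**What the plan says.** The Statistical analyses section of the protocol article sets out a sequence.

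- First, the arms are compared at baseline: "Analyses will first be performed to evaluate the comparability of the RGCT and the UC groups at study entry". The comparison covers sociodemographic and clinical characteristics, and the tool is a test: "Student's t-test or appropriate non-parametric statistics will be used, depending on the level of measurement".
- The result then drives the later models: "If the groups are not comparable on one or more background variables, those variables will be employed routinely as covariates in subsequent analyses".
- Choice of surgery, the primary outcome, is "tested using the chi-square statistic or, if statistical adjustment is required for covariates, multiple logistic regression analysis".
- For the questionnaire outcomes, analysed by analysis of (co)variance at 6 and 12 months, there is a second route: "Where appropriate, sociodemographic and clinical background variables, as well as baseline scores on the outcomes of interest, will be used as covariates".

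The section gives no threshold for calling the groups not comparable and does not say how many variables are tested. It names no individual background covariate in advance. Hospital, by which randomisation is stratified (Recruitment and randomization), is not mentioned as a covariate.

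**The concern.** Allocation is computerised, and the sequences are unknown to the researchers until the patient is randomised. Baseline differences between the arms as randomised are therefore chance differences, and a test of them has no hypothesis to answer. Nor does the test show which variables predict the outcome. A variable unrelated to surgery choice can enter because it happens to differ, while a strong predictor that happens to balance stays out.

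More is at stake than tidy reporting. Whether the main result comes from an unadjusted comparison of proportions or from a conditional odds ratio depends on the chance pattern at baseline. The article states this rule outright, so it is not a detail left to an analysis plan.

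**Working it through.** **1. The plan's own figures.** The Sample size section claims "80% power to detect a difference of 18% versus 5% in the uptake of bilateral mastectomy, with the p-value set at 0.05" with 170 and 85 women. The 18% follows from its assumptions: 0.20 × 0.50 + 0.80 × 0.10 = 0.18. A two-proportion formula (two-sided 5%, 80% power, 2:1) with continuity correction gives 86 in usual care, or 258 in total, close to the stated 255. Without the correction it gives 74 (222 in total), and power at 85 and 170 is 85.9%. The sample size does not depend on the covariate rule and reproduces.

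Expected bilateral mastectomies: 0.18 × 170 = 30.6 and 0.05 × 85 = 4.25, about 35 in all.

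**2. How often the primary test would switch by chance.** Assumptions: each variable is tested at 5%, and the tests are independent. The study measures list about ten candidates (age, education, marital status, ethnicity, work, general health, pedigree, genetic risk, diagnosis, tumour characteristics), so 10 to 15 is a reasonable range.

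| Variables tested | At least one: 1 − 0.95^k | Exactly one: k × 0.05 × 0.95^(k−1) | Two or more |
|---|---|---|---|
| 10 | 0.401 | 0.315 | 0.086 |
| 15 | 0.537 | 0.366 | 0.171 |

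Among trials that switch, one covariate is responsible in 0.315/0.401 = 79% and 0.366/0.537 = 68% of cases. With only 5 variables the chance of a switch is 23%.

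**3. Binary primary outcome.** Simulation at 85 and 170, 10,000 trials per setting, with 1 or 5 covariates at odds ratios of 1.5 to 4 per SD (assumed). The adjusted test is the logistic likelihood-ratio test. Simulation error on the size is about 0.002.

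| Analysis | Size, 5% in both arms | Size, 13.7% in both arms | Power, 5% vs 18% |
|---|---|---|---|
| Chi-square | 0.045–0.046 | 0.045–0.054 | 86.9–87.7% |
| Two-stage rule | 0.045–0.049 | 0.042–0.053 | 87.8–88.2% |
| Always adjusted | 0.060–0.066 | 0.050–0.059 | 90.9–94.3% |

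The two-stage rule behaves much like a plain chi-square. Part of the apparent gain from always adjusting comes from the liberal size of the likelihood-ratio test at low event rates.

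**4. Continuous outcomes.** One covariate with correlation ρ to the outcome, adjusted for only when its baseline test is significant at 5%.

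- *Size.* Two-stage: 0.047 at ρ = 0.3, 0.044 at 0.5 and 0.035 at 0.7. Always adjusting: 0.049 to 0.050.
- *Power at 0.3 SD, analytic check.* The unadjusted signal is 0.3 × √(85 × 170/255) = 2.26 standard errors, so power is about Φ(2.26 − 1.96) = 0.62. Always adjusting divides the standard error by 1/√(1 − ρ²). This gives about 0.63 at ρ = 0.2, 0.66 at 0.3 and 0.81 at 0.6.
- *Power at 0.3 SD, simulation.*

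| ρ | Two-stage | Always adjusted | Loss (points) |
|---|---|---|---|
| 0.2 | 61.3% | 62.9% | 1.6 |
| 0.3 | 62.1% | 65.4% | 3.3 |
| 0.6 | 62–63% | 80% | about 17 |

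**5. Logistic regression with hospital terms.** There are 12 hospitals, so 11 extra parameters on about 35 events. If the hospitals were of equal size (assumed), each would have about 14.2 RGCT and 7.1 usual-care patients. The chance of no event in a given hospital is 0.82^14.2 × 0.95^7.1 ≈ 0.042. The chance that at least one of the 12 has none is then about 1 − 0.958^12 ≈ 0.40. That is a poor basis for a maximum-likelihood model.

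**The case against.** The strongest counter-argument is that the rule does little measurable harm to the primary outcome. This stands: size is near nominal, power is about that of the chi-square test, and both exceed the planned 80%.

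It is also fair that the tested rule covers only sociodemographic and clinical characteristics. Baseline scores have their own sentence. A correlation of 0.6 is plausible for a baseline score but not for education or marital status, so the 17-point loss is not the expected cost of the rule. It would arise only if the loose where-appropriate wording let a baseline score be left out unless it was imbalanced. At the article's own 0.5 SD target, unadjusted power is already about 96%.

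A reader might infer that selecting covariates after testing inflates the type I error. The calculations show the opposite: where size departs from 5% under the two-stage rule, it is mainly downwards. A reader might also infer that the article switches away from a declared risk difference. It declares none and says only that effect sizes will be calculated by standard procedures. Finally, one might expect an overloaded logistic model, but three or more chance-selected covariates would be rare.

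What the objection does not remove is that the primary test depends on observed imbalance, for no gain over a fixed choice.

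**Conclusion.** The point holds as a fault of pre-specification and efficiency, not of error control. The article lets chance imbalance select the covariates and the primary test. Under the assumed 5% threshold and 10 to 15 independent variables, the switch would happen by chance in 40% to 54% of trials. Correlated variables or another threshold would change that figure.

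For the binary primary outcome the effect on size and power is small, and the harm is that the test and the estimate that goes with it are open until the data are seen. For questionnaire outcomes the loss is about 2 to 3 power points at 0.3 SD for moderately prognostic background variables. It is larger only if baseline scores were treated the same way. This is a cheap improvement that should be made; it does not threaten the validity of the trial.

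**What to change.** Replace the comparability rule with text to this effect:

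- Baseline characteristics are tabulated by arm without significance tests.
- Choice of surgery has one primary analysis, fixed in advance. Examples are a chi-square test with a risk difference and 95% confidence interval, or a Mantel-Haenszel risk difference stratified by hospital. A logistic model with 12 hospital categories is not suitable with about 35 expected events.
- Each questionnaire outcome is analysed by ANCOVA that always includes the baseline score, where one was collected, and hospital as the stratification factor.
- Any other covariate is measured before randomisation, chosen for prognostic value, and named before outcome data are analysed.
- Adjustment for observed imbalance may be reported as a sensitivity analysis.

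The cost is a few sentences of wording, with no extra patients or data. The small downside is that the main analysis can no longer be adjusted ad hoc for a striking chance imbalance; the sensitivity analysis covers that case.
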